### Adverse events

The occurrence of adverse events from all interventions will be monitored and assessed using case report forms, contact with the trial coordinator, physiotherapist report, and follow-up questionnaires. However, as the intervention is the introduction of a direct access pathway and the treatments received will be the same as in usual clinical practice, adverse events are unlikely. Physiotherapists and GPs will report any serious adverse event (SAE) experienced by a trial participant immediately to the trial chief investigator that may possibly be related to either the interventions or the trial procedures. The chief investigator will assess whether the event was related to or resulted from any of the STEMS study trial interventions or procedures. Any SAE considered to be related to the trial procedures or interventions will be reported to the main Research Ethics Committee by the chief investigator within 15 days of her becoming aware of the event. In addition, all such events will be reported to the trial sponsor, Trial Steering Committee and Data Monitoring Committee.

### Safety of direct access to physiotherapy

Any serious or significant pathologies that would require urgent medical assessment missed by physiotherapists in patients who directly access care will be reported. Physiotherapists and GPs will be asked to report any cases they become aware of. In addition, a systematic search of the GP medical record for participants who consent to medical record review and who directly access physiotherapy care will be undertaken to identify any possible cases of missed serious or significant pathology. The number of missed serious pathologies will be described only for participants directly accessing physiotherapy.

### Sample size

As this is a pilot trial, a formal sample size calculation has not been carried out. Using Keele’s Consultation in Primary Care Archive (CiPCA) database of GP practices and symptom and diagnostic Read codes, 25 % of the population in an average-sized GP practice (5000 patients) consults at least once per year with a musculoskeletal problem (1250 patients or 100 patients per month). Given the trial exclusions, we anticipate at least 80 % of consulters to be eligible (80 patients per month per practice), 50 % to respond to the invitation to take part in the research evaluation, provide consent and complete a baseline questionnaire (40 patients per month per practice). With four practices recruiting for 6 months in the pilot trial, we estimate 960 participants at baseline and 80 % follow-up (*n* = 768).

### Analysis

Since this is a pilot trial, the analyses will focus on describing the key process measures in order to decide if a main trial is feasible and desirable, in addition to finalising the sample size for a future main trial.

#### Determine engagement of GP practices and the physiotherapy service

The number of GP practices and physiotherapy services that have agreed to participate in the trial will be recorded and presented as a proportion of the number of eligible practices approached. Information will be presented that summarises GP practice characteristics (full-time equivalent of GP staff, number of patients and number of adults registered at practice and GP consultation rates for musculoskeletal patients before and during pilot trial recruitment as well as the physiotherapy team characteristics (full-time equivalent staff and their clinical grades).

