#### Process objectives

To assess the number of practices approached and agreeing to take part (baseline) and the engagement of GP practices and physiotherapy services to stay in the pilot trial through follow-up (12 months)To develop and test approaches to market a new direct access service in ways that ensure a sufficient proportion (at least 20 %) of patients access physiotherapy through self-referral to make a main trial feasible (assessed through referral methods as physiotherapy service)To assess the feasibility of establishing a physiotherapy direct access service that can respond to demand and avoid increases in waiting times or staffing levels (monitored throughout the recruitment period)To estimate participant recruitment rates in both control and intervention practices (assessed at end of recruitment)To explore any evidence of selection bias in participants recruited to the research evaluation from the control and intervention practices (assessed through participant characteristics at baseline)To estimate retention of participants in the research evaluation at each follow-up time-point across both control and intervention practices

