### Setting and clusters

The setting is primary care in England for adults with musculoskeletal problems (GP practices and linked NHS physiotherapy services). GP practices are the unit of randomisation, and thus, patients follow the care pathways to which the practice is randomised. In this pilot, RCT practices will be stratified only on practice size, but in a main trial, practices would also ideally be stratified by index of deprivation. Randomisation of GP practices will be undertaken by an independent statistician. GP practices will be randomised to one of two arms, either to continue with usual GP-led primary care for musculoskeletal patients with the addition of the offer of a self-referral physiotherapy pathway (intervention group) or to continue with usual GP-led primary care alone (usual care control group). Practices will be randomised according to a computer-generated random numbers stratified by the practice size (small or large) in the ratio 1:1. In a main study, we would plan to further stratify by practice setting and area level deprivation (through minimisation) in order to ensure balance in key practice characteristics in each arm of the trial.

GP practices are eligible to take part if they meet the following criteria: they are within the Vale Royal Clinical Commissioning Group area of Cheshire and the Clinical Research Network (CRN); they are a group practice, currently referring musculoskeletal patients to NHS physiotherapy services; they do not currently offer direct access to physiotherapy; and they are willing to test direct access. The balance between scientific considerations and the need for consent is a known issue for cluster trials [27]. Informed consent for practices to participate will be provided by the senior GP partner in each practice acting as ‘guardian’ for patients in their care. Patients will follow the care to which their practice is randomised with identical patient information for both arms providing general information about the study, explaining that their local musculoskeletal services are being evaluated using patient self-reported clinical outcomes and medical record review. Individual patients will therefore be able to opt out of data collection.

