### Outcome measures

Process outcomes: Process outcomes will determine if a future main trial is possible and desirable. Anonymised process outcome data will be collected from GP records and physiotherapy administration databases and self-referral forms. Health service process outcomes include the proportion of patients not referred to physiotherapy services, those referred to physiotherapy and the number of patients directly accessing physiotherapy in the intervention practices, proportion of ‘recommended self-referral’ and ‘true self-referral’ in the direct access pathway, waiting times for treatment (time from logging of referral to first physiotherapy appointment), number of GP and NHS physiotherapy consultations for musculoskeletal problems and non-attended physiotherapy appointments (DNA rates). Research process outcomes include estimation of recruitment rates, exploration of evidence of selection bias and follow-up rates at each time-point with differences in the control and intervention practices explored to identify sources of bias. A summary of the process measures is shown in Table 1.

**Table 1 Tab1:** STEMS pilot trial process measures

Engagement of GP practices and PT services
Physiotherapy site recruitment rate to participate in STEMS study
GP Practice recruitment rate to participate in STEMS study
Research evaluation
Recruitment rate to the research evaluation—all adults with musculoskeletal conditions
Recruitment rate to the research evaluation—‘true self-referral’^a^ patients
Recruitment rate to the research evaluation—‘recommended self-referral’^b^ patients
Retention rates to research evaluation at 2, 6 and 12 months follow-up
GP practice characteristics
Number of GPs and nurse practitioners per practice
Number of patients and number of adults registered at practice
GP consultation rates for adults with musculoskeletal conditions (before and during study)
Physiotherapy team characteristics
Number of physiotherapists working in the physiotherapy service (in total and STEMS trained)
Seniority of physiotherapists in the physiotherapy service (in total and STEMS trained)
Physiotherapy service
Physiotherapy service GP referral rate (before and during study)
Physiotherapy service ‘true self-referral’^a^ rate
Physiotherapy service ‘recommended self-referral’^b^ rate
Non-attendance rates at physiotherapy site for GP referrals (before and during study) and for self-referrals during study

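### Practice uptake is to be reported among eligible practices approached, but eligibility includes willingness to test direct access, so the rate can only be biased upward

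*Protocol article*

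**What the plan says.** Four places in the protocol article bear on practice engagement.

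- **Process objectives.** The first objective covers the practices approached and those agreeing at baseline, together with their staying in the trial to 12 months. It asks for numbers and defines no proportion.
- **Analysis, Determine engagement of GP practices and the physiotherapy service.** On what is counted, this part of the plan states: "The number of GP practices and physiotherapy services that have agreed to participate in the trial will be recorded". The result is to be "presented as a proportion of the number of eligible practices approached".
- **Setting and clusters.** The eligibility list has structural items (location in the named commissioning area and research network, being a group practice, referring to NHS physiotherapy). It closes with: "they do not currently offer direct access to physiotherapy; and they are willing to test direct access". Agreement to join is a further step: "Informed consent for practices to participate will be provided by the senior GP partner in each practice".
- **Outcome measures, Table 1.** The measure is listed as "GP Practice recruitment rate to participate in STEMS study", with no denominator. The physiotherapy-site rate has its own line.

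**The concern.** A participation rate should be taken over units that were free to say yes or no. One of the eligibility conditions here is itself a form of saying yes. If eligible in the analysis section means what the eligibility list says, a practice that refuses because it does not want direct access is removed from the denominator and cannot lower the rate.

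The Objectives section says the process objectives focus on the feasibility of working with practices to set up direct access and on its acceptability. Practices' willingness is part of that, and the planned percentage conditions on it. Practices are also the units of randomisation. Anyone using this percentage to judge how many practices a main trial would need to approach would start from a figure that is too high whenever some refusals were for unwillingness.

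**Working it through.** **The plan's own figures.** The article states no practice-uptake figure, so there is none to reproduce. The nearest calculation is the participant projection under Sample size: 100 consulters per month × 0.80 eligible × 0.50 responding = 40 per practice per month; 40 × 4 practices × 6 months = 960; 960 × 0.80 = 768. Both totals match the article. They matter here only because they fix the number of practices taking part at four.

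**Inputs for uptake.**

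- Practices agreeing: 4 (Sample size).
- Practices approached, A: not given. Assumed to be 5 to 12, for illustration only.
- Refusals: A − 4.
- Refusals because the practice will not test direct access, U: not given. Varied from 0 to A − 4.
- All practices approached are assumed to meet the structural criteria.

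**Formulas.**

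- Uptake on all approached = 4 / A.
- Uptake on eligible practices approached, applying the eligibility list literally = 4 / (A − U).

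Since U ≥ 0, the second is never smaller than the first. They are equal only when U = 0, and the second reaches 100% only when U = A − 4, that is, when every refusal is for unwillingness.

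**Main illustration, A = 8 (four refusals).**

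| Refusals for unwillingness (U) | All approached | Eligible practices approached |
|---|---|---|
| 0 of 4 | 4/8 = 50% | 4/8 = 50% |
| 1 of 4 | 50% | 4/7 = 57% |
| 2 of 4 | 50% | 4/6 = 67% |
| 3 of 4 | 50% | 4/5 = 80% |
| 4 of 4 | 50% | 4/4 = 100% |

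**Other assumed values of A.**

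- A = 5: 4/5 = 80% on all approached; 4/4 = 100% if the single refusal is for unwillingness.
- A = 6: 4/6 = 67% on all approached; 4/5 = 80% if one of the two refusals is for unwillingness, and 100% if both are.
- A = 12: 4/12 = 33% on all approached; 4/10 = 40%, 4/8 = 50% and 4/6 = 67% if two, four or six of the eight refusals are for unwillingness, and 100% if all are.

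The direction is fixed by the definition. The size depends entirely on A and U, which the article does not give.

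**Numerator.** The same analysis sentence counts agreeing physiotherapy services together with practices, but its denominator names practices only. Table 1 keeps the two rates apart.

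**The case against.** The strongest case against the point has four parts.

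1. **Eligible may mean structurally eligible.** Willingness can hardly be known before a practice is approached, so the authors may have meant practices that qualified to be approached on location, type and referral pattern. Nothing says that a practice which declines is reclassified as ineligible. This reading is possible and lowers confidence. However, the eligibility list puts willingness on the same footing as the other criteria, and nothing in the article keeps unwilling practices in the denominator.
2. **The counts are planned anyway.** The first process objective covers both the number approached and the number agreeing, so agreed over approached could be worked out from them. This stands, and confines the defect to the one percentage that the analysis section specifies.
3. **Willingness is not consent.** A practice may be willing to test direct access and still decline because of randomisation, record downloads or workload, and the senior partner's consent is a separate step. Such refusals stay in the denominator on either reading. This also stands.
4. **Little depends on the rate.** The article sets thresholds for participant recruitment (40%), retention at 6 months (70%) and the share of caseload through direct access (20%), but none for practice uptake. This stands and keeps the severity low.

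A reader might also infer that the objective and the analysis contradict each other. They do not: the objective asks for counts, and the analysis forms a proportion over a subset of the practices approached.

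**Conclusion.** The point holds as a minor one, with moderate confidence. Under the eligibility criteria as written, the planned denominator leaves out practices that refuse because they will not test direct access. The reported uptake is therefore at least as high as agreed over approached. With 4 agreeing of an assumed 8 approached, the figure would be 57% to 100% in place of 50% if between a quarter and all of the refusals were on that ground, and unchanged if none were.

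This rests on a literal reading of the eligibility list and on an assumed number approached. It does not show that uptake must approach 100%, which is the limiting case in which every refusal is for unwillingness. Nor do the documents support saying that unwillingness is practices' main reason for declining. The Background names the medical profession as both a barrier to and a facilitator of direct access, and does not rank reasons for refusal. For the same reason, no definite multiple can be given for how far a main trial's approach list would fall short.

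**What to change.** In the analysis section on engagement, change the denominator to all practices approached that meet the structural criteria: within the named area and research network, a group practice, referring to NHS physiotherapy, and with no existing direct access. Treat unwillingness to test direct access as a reason for refusal. Report the numbers approached and agreeing, with refusals by reason. Give the physiotherapy-service rate separately, as Table 1 already does.

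The change is about one sentence. The number approached is already needed for the first process objective. Reasons for refusal have to be noted when practices decline, as they are hard to recover later. The drawback is that the reported uptake may be less favourable.

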#### Feasibility of study recruitment and retention

The number of participants identified and recruited using each recruitment method will be reported, along with the number of participants followed up at each time-point. Withdrawals (and where possible, reasons for withdrawals) will be reported. A priori, we have defined a success criterion of 40 % of the total number of participants invited to be recruited to the research evaluation. Whilst a retention rate of 100 % would be ideal, we will consider a rate of 70 % at 6 months follow-up satisfactory. We will provide the point estimate of the proportion and its 95 % confidence interval (CI). Difference in recruitment uptake rate and follow-up rates at each time-point will be compared between the intervention and control arms.

#### Feasibility of direct access

An audit of the feasibility of offering direct access will be conducted using anonymised data. This will include reporting the number of participants who are referred to physiotherapy by their GP, those who are ‘recommended self-referrals’ (prompted by their GP or practice nurse to refer) and those who are ‘true self-referrals’ and the waiting time to the first physiotherapy appointment. Figures will be presented month-by-month for patients using direct access as well as the overall totals. The proportion of patients directly accessing care (true and recommended self-referrals) compared to all referrals received at the physiotherapy site will be calculated to check the success of marketing the direct access service. The aim is to ensure that a minimum of 20 % of the total physiotherapy caseload during the pilot trial, from practices randomised to the intervention arm, is through direct access. In order to assess the feasibility of establishing a direct access service that can respond to demand, descriptive measures of the total number of referrals received from participating practices and staffing levels in the participating physiotherapy department will be used to establish how the physiotherapy service responds to demand through waiting time for first physiotherapy appointment. The source by which patients, who access care directly, become aware of the direct access service will be presented and compared in order to establish which methods (GP advised, poster, individual mailing, heard from a friend and other methods) are most successful in marketing the service.

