## Background

Musculoskeletal problems are common and costly and increase with age. Musculoskeletal conditions account for up to 30 % of general practitioner (GP) consultations [1], and yet it is estimated that only between 30–40 % of individuals with musculoskeletal problems consult their GP [2–4]. The Global Burden of Disease Study shows that musculoskeletal conditions are a major cause of chronic disability worldwide and have increased markedly in the last decade [5]. Given the ageing population and the increasing impact of these common painful conditions, the demand for musculoskeletal healthcare is set to rise and health care delivery systems will need to develop a ‘coherent policy for dealing with musculoskeletal disorders’ [5]. Best evidence for many of these musculoskeletal conditions recommends treatments such as advice, education, exercise, manual therapy and acupuncture [1, 6, 7]. Such treatments are cost-effective [8] and are those that professionals such as physiotherapists are equipped to deliver. Early physiotherapy intervention for musculoskeletal problems reduces sick leave and helps prevent acute problems becoming chronic [1, 9–12]. However, for most patients in the UK, access to National Health Service (NHS) physiotherapy is controlled through GP referral.

Direct access to physiotherapy is a system of access in which ‘patients are able to refer themselves to a physiotherapist directly without having to see anyone else first or without being told to refer themselves by a health professional’ [13]. Although direct access is well established in private practice in the UK and in other countries including Australia, the Netherlands, some states within the USA and in Scotland [14–17], uptake in the NHS in England has been very limited. Funders of physiotherapy services express concerns about creating excessive demand and associated costs and where direct access services have been established at least one in England has been stopped due to funding being withdrawn [18].

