### Description of intervention and control arms

Control practices: In GP practices allocated to the control arm patients will continue to be managed according to usual GP-led care. This normally consists of a patient consulting their GP and receiving advice and treatment (often medication but we expect around 20–25 % to be referred to physiotherapy, or for a diagnostic test or other treatment service). For some patients, it may mean being triaged by a practice nurse and managed with advice and/or referral to physiotherapy or other services. Usual GP-led care therefore includes all of these pathways in participating GP practices but will not include the offer of direct access to physiotherapy. No additional information on physiotherapy services will be disseminated by the research team to GP practices delivering usual care. Regular contact with, and feedback to, the control practices through CRN staff, a GP research facilitator and from the PI and study team will help ensure smooth trial operationalisation.

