### Design considerations and limitations

We acknowledge that a limitation of the trial design is recruiting patients in the control arm from GP practices and in the intervention arm from GP practices and the physiotherapy service. In an ideal design, we would compare all patients who have a musculoskeletal problem registered with participating practices during the study period, whether or not they attend their GP and/or physiotherapy service but clearly this is not possible. Other trial designs were considered, but these would have led to greater differences in patients recruited to the two arms of the trial. We will therefore make considerable efforts to identify any evidence of selection and recruitment bias between the arms of the pilot trial, although we acknowledge that patients may differ on other unknown factors.

It is possible that over time, as patients become accustomed to direct access, their expectations and service use may change. Clinical outcomes are unlikely to change beyond 12-month follow-ups, but costs and benefits may change as direct access becomes established within a community. Therefore, this pilot trial includes follow-up to 12 months as longer follow-up would be expensive within the context of a trial.

This pilot aims to inform a main trial with a non-inferiority design as the addition of a direct access to physiotherapy pathway is not anticipated to be superior in terms of patients’ clinical outcomes. However, a range of secondary outcomes is included that in a main trial will provide important information for patients, health care practitioners and commissioners if clinical non-inferiority is demonstrated. Previous work suggests an effect size of 0.2 to 0.6 as a minimum clinically important difference, and we would thus, anticipate specifying a difference between groups of 0.2 as the threshold for the purposes of demonstrating non-inferiority in a main trial.

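### The proportion planned as a check on the 20% direct-access target uses a different denominator from the target, pools prompted with true self-referrals, and does not show how little of the intervention arm the target implies

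*Protocol article*

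**What the plan says.** The Process objectives want at least 20% "of patients access physiotherapy through self-referral to make a main trial feasible". Outcome measures adds that process outcomes will determine whether a main trial is possible and desirable.

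Feasibility of direct access, in the Analysis section, gives the operational version in two consecutive sentences. The first describes the calculation: "The proportion of patients directly accessing care (true and recommended self-referrals) compared to all referrals received at the physiotherapy site will be calculated". Its stated purpose is to check how well the marketing worked. The second gives the target, a minimum of 20% "of the total physiotherapy caseload during the pilot trial, from practices randomised to the intervention arm, is through direct access".

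Other parts of the protocol article bear on how this reads:

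- Methods for protecting against sources of bias says that the same physiotherapists treat patients from both arms, and that the comparison is between all musculoskeletal consulters in each arm.
- The Background defines direct access thus: "patients are able to refer themselves to a physiotherapist directly without having to see anyone else first or without being told to refer themselves". The definition names health professionals as the source of any such instruction.
- Description of intervention and control arms separates GP- or nurse-recommended self-referral from true self-referral. Feasibility of direct access and Results and discussion use the labels in the same sense. The footnotes to Table 1 attach the prompted definition to true self-referral and the unprompted definition to recommended self-referral.
- For usual care, around 20-25% of patients are expected "to be referred to physiotherapy, or for a diagnostic test or other treatment service".
- For the main trial, Design considerations and limitations says: "we would thus, anticipate specifying a difference between groups of 0.2 as the threshold for the purposes of demonstrating non-inferiority in a main trial".

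**The concern.** The 20% figure is the one measure of intervention uptake that the protocol article ties to the feasibility of a main trial. Three things weaken it.

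1. **Denominator.** The calculation described is not the one that the target needs. Control practices have no direct-access route, so their referrals add to the denominator and never to the numerator. A reader who sets the calculated proportion against 20% would understate uptake.
2. **Numerator.** Pooling the two kinds of self-referral lets the target be met by GPs asking patients to fill in a form in place of a written referral. Under the Background definition that is not direct access. With the Table 1 labels reversed, a separate tabulation could also be misread.
3. **Level.** The target describes the physiotherapy caseload, while the main trial would compare whole arms of consulters. A modest share of caseload becomes a very small share of an arm. That bears on whether a whole-arm non-inferiority comparison says much about those who use the route.

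**Working it through.** **The plan's own projection.** From Sample size: 100 consulters per practice per month x 0.80 eligible x 0.50 recruited = 40. Then 40 x 4 practices x 6 months = 960, and 960 x 0.80 = 768. Both stated figures reproduce. Randomisation is 1:1, so equal recruitment gives 480 per arm. The document states no expected share of the intervention arm using direct access.

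**Denominator.** Assume that each arm would generate 100 GP referrals and that the site receives only trial referrals.

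- Self-referrals replace GP referrals: intervention caseload is 100, of which 20% = 20 are direct access. Site total is 200, and 20/200 = 10%.
- Self-referrals add to GP referrals: 25 direct-access patients give 25/125 = 20% of intervention caseload. Site total is 225, and 25/225 = 11.1%.

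If the site also took referrals from outside the trial (assumption; the document does not say), the replacement figure falls further: 0.20 x 0.5 x 0.75 = 7.5% if a quarter come from outside, and 0.20 x 0.5 x 0.5 = 5% if half do.

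**Numerator.** Let t be the fraction of direct-access patients who are true self-referrers. True self-referral as a share of intervention caseload, when the pooled figure is exactly 20%, is 0.20 x t:

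| t | True self-referral, % of intervention caseload |
|---|---|
| 0 | 0 |
| 0.25 | 5 |
| 0.5 | 10 |
| 1 | 20 |

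The target sets no minimum for t.

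**Share of the arm at the minimum.** Let r be the share of consulters referred to physiotherapy, taken as 20-25% and read as physiotherapy alone.

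- Replacement: 0.20 x r. This gives 0.20 x 0.20 = 4.0% and 0.20 x 0.25 = 5.0%, or 19 and 24 of 480.
- Additional demand: 0.25r / (1 + 0.25r). This gives 0.05/1.05 = 4.8% and 0.0625/1.0625 = 5.9%, or 23 and 28 of 480.

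The range is therefore about 4-6%. The sentence giving 20-25% can also be read as covering tests and other services. If r for physiotherapy alone were 10-15% (assumption), the share would be 2.0-3.0% with replacement and 2.4-3.6% with additional demand.

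**What that means against the margin.** Suppose, for illustration, that the route affects only its users. An arm-level difference of 0.2 SD would then need an effect among users of 0.2/p, where p is the share using it. That is 0.2/0.05 = 4 SD to 0.2/0.04 = 5 SD with replacement, and 0.2/0.059 = 3.4 SD at the top of the additive range.

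**The case against.** **The 20% has only one denominator.** A reader might infer that the criterion has two and could pass or fail according to which is chosen. The text does not support that. The 20% is attached only to intervention-practice caseload, and the all-site proportion is a check on marketing that carries no threshold. What stands is that this check, placed immediately before the target, does not measure it.

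**It is an aim.** The analysis section calls the 20% an aim and states no stopping rule, so calling it a go/no-go rule goes beyond the document. The link to main-trial feasibility in the Process objectives does stand.

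**Prompted self-referral is a declared part of the pathway.** The Methods describe both routes and report them separately, along with how patients heard of the service. A result made up wholly of prompted referrals would be visible. The narrower definition is quoted in the Background from a cited source. What stands is that the two definitions conflict and that the target is blind to the mix.

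**Low uptake is part of the question.** The comparison is of the additional offer at practice level, by intention to treat, and the protocol openly expects many patients to keep consulting their GP. Self-referrers are compared descriptively with control patients referred to physiotherapy, and records of direct-access users who consent to review are searched for missed serious pathology. Preferring direct access would require other benefits besides non-inferiority. This is a fair defence of the design. It does not remove the need to know the share of the arm that used the route when the margin is judged.

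**The 4-6% is an inference.** It takes the 20% as achieved uptake when it is a floor, applies a control-practice figure to the intervention arm, and carries a service-level share over to research participants as if uptake to the evaluation were equal by pathway. These caveats stand.

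**Conclusion.** The point holds as a misalignment that should be corrected. The calculation described does not measure the target: 20% of intervention caseload would appear as about 10-11% of two-arm site referrals, assuming equal referral volume per arm and no outside referrals. The pooled numerator allows the target to be met with no direct access in the Background sense, and the Table 1 footnotes contradict the text on which patients are which. At the minimum, direct access would be used by about 4-6% of the intervention arm. That rests on the 20-25% meaning physiotherapy alone and on equal recruitment by pathway; the share is lower if the figure covers other services.

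Two stronger conclusions are not supported. A reader might infer that everyone else in the intervention arm receives exactly the care that control patients receive. The document does not show this, since practice-wide marketing and changes in waiting time could reach non-users. A reader might also infer that the target should be 20% of all participants. Under replacement that would need 0.20/0.25 = 80% to 0.20/0.20 = 100% of physiotherapy caseload. Under additional demand, 25 direct-access patients per 100 GP consulters give 0.25/(0.25 + 0.25) = 50% to 0.25/(0.20 + 0.25) = 56%. The Background cites 22-28% of referrals from an observational evaluation in the Netherlands. Such a bar would in effect reject the main-trial design, and nothing in the document calls for it.

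**What to change.** 1. Calculate the direct-access proportion with physiotherapy referrals from intervention practices as the only denominator for the 20% target, and drop the all-site version as its check. Bring the looser wording of the Process objective into line.
2. Reconcile the numerator with the Background definition by showing the result against 20% twice: for true self-referrals alone, and for true plus recommended self-referrals.
3. Correct the Table 1 footnotes so that the labels match the rest of the text.
4. Report direct-access users as a share of all intervention-arm participants, and use that share when judging whether the anticipated 0.2 SD margin is informative for the main trial.

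The cost is wording and a few extra proportions, because each patient's pathway is already to be recorded. The downside is that the feasibility result may look less favourable, above all if most self-referral turns out to be prompted.
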